## Methods/design

### Aim

The proposed research will evaluate the efficacy of a pamphlet-based personalized feedback intervention for problem drinkers in the general population.

The hypotheses regarding the efficacy of the pamphlet-based intervention are:

Hypothesis 1: Respondents from households who receive the personalized feedback pamphlet-based intervention will display significantly improved drinking outcomes at three and six-month follow-ups as compared to respondents from households in the no intervention control condition.

Hypothesis 2: Respondents from households who receive the personalized feedback pamphlet-based intervention will display significantly improved drinking outcomes as compared to respondents from households who receive the control pamphlet.

In addition, two mediator hypotheses will be tested:

Hypothesis 3: Respondents who receive the intervention and reduce their estimates about how much others drink between baseline and three-month follow-up will display significantly improved drinking outcomes at six-month follow-up as compared to respondents who receive the intervention but experience no decrease in their perceived drinking norms.

Hypothesis 4: Respondents who receive the intervention and experience an increase in their perceived vulnerability to experience harm because of their alcohol consumption between baseline and three-month follow-up will display significantly improved drinking outcomes at six-month follow-up as compared to respondents who receive the intervention but experience no increase in their perceived risk.

Finally, two moderator hypotheses will be tested:

Hypothesis 5: The impact of the intervention will be greater among drinkers who believe that they are personally vulnerable to negative outcomes at baseline assessment, compared to drinkers who do not believe that they are personally 'at risk' before receiving the intervention.

Hypothesis 6: Respondents who drink for social reasons will be more likely to reduce their drinking as a result of the intervention as compared to respondents who do not drink for social reasons.

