### Do personalized alcohol feedback interventions work because they modify perceived drinking norms?

Several researchers have applied self-regulation theory [50] as a model to help explain the impact of personalized feedback interventions [32,51,52]. By overestimating the prevalence of heavy consumption among peers, heavy drinkers are thought to view their own behavior as normative rather than abnormal or inappropriate. Personalized normative feedback is theorized to develop discrepancy in the recipient by providing information showing that their own drinking is not normative [41,45,53]. Alerting heavy drinkers to the fact that their own drinking is abnormal (i.e., developing discrepancy) is theorized to result in problem recognition and may instigate behavior change [44,51,54]. If this process does mediate the impact of normative feedback interventions then, for the intervention to work, it must modify recipients' perceptions of how much others actually do drink. The modification of these perceptions would then lead to an increase in perceptions of discrepancy between their own and others' drinking. Because of the importance of understanding why normative feedback interventions work, the current study will include perceived drinking norms as a hypothesized mediator of the impact of the personalized feedback pamphlet intervention.

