### Design

In an initial telephone interview, sociodemographic information will be collected. Current drinkers will complete a standardized epidemiological assessment of problem drinking and alcohol consumption, and will answer items to assess their perceived drinking norms, their perceived risk regarding drinking and their social reasons for drinking. Respondents identified as problem drinkers will be asked if they are willing to participate in a three-month and a six-month follow-up. Respondents will be offered a $20 honorarium for completion of each of the three-month and six-month follow-ups. Verbal informed consent will be gathered and respondents will be told that some households will be receiving a pamphlet. Problem drinking will be defined as a score of eight or more on the Alcohol Use Disorders Identification Test (AUDIT) [64,65]. The initial telephone survey will be conducted with a random sample of respondents from households within a major metropolitan city in Canada. One current drinker 19 years or older (legal drinking age in Ontario, Canada) will be selected to participate from each household by soliciting participation from the adult in the household who had the most recent birthday who also drinks alcohol at least once per month. All households with respondents agreeing to participate in the follow-up interviews will be randomized into three groups – personalized feedback pamphlet condition, control pamphlet condition and no intervention control condition. In the week after the baseline survey, all households that contain respondents in the two pamphlet conditions will be sent their respective pamphlets. Three months after the intervention mailing, respondents who agree to the follow-ups will be administered a second telephone interview assessing the same drinking and mediator terms as the baseline survey (modified to refer to the past three months). Similar drinking outcome measures will be made six months after the intervention mailing with the items framed to refer to the past three-months. In order to ensure that all study participants receive some form of intervention, households in the no intervention control condition will be sent the personalized feedback intervention pamphlet after the six-month follow-up.

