### Three-month Follow-up Survey

The three-month follow-up will occur roughly three-months after the intervention pamphlet is sent (or equivalent time for those in the control condition).

(1) Drinking in the last three months will be assessed using the same five items employed on the baseline survey, the first four framed for the past three months (frequency of consumption, drinks per occasion, frequency of 5+ consumption, highest number of drinks on one occasion) and the last asking how much the person drank on each day of the last week.

(2) Six items assessing whether in the past 3 months alcohol had a harmful effect on respondents' (1) friendships/social life, (2) physical health, (3) outlook on life (happiness), (4) home life or marriage, (5) work, studies, or employment opportunities, or (6) financial position [68].

(3) Mediator variables, perceived drinking norms and perceived risk will be measured using the same items as on the baseline survey.

(4) Formal addictions treatment utilization will be measured using the same single item as the baseline survey, modified to ask about the last three months.

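### Hypotheses 3 and 4 are called mediator hypotheses but are worded as non-randomised comparisons within the intervention arm, so they do not test whether the pamphlet moves the mediator

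*Protocol article*

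**What the plan says.** The Aim section announces that "two mediator hypotheses will be tested". Hypothesis 3 takes respondents who receive the intervention and lower their estimate of others' drinking between baseline and three months. It predicts better six-month drinking for them "as compared to respondents who receive the intervention but experience no decrease in their perceived drinking norms". Hypothesis 4 predicts the same for those whose perceived vulnerability rises, "as compared to respondents who receive the intervention but experience no increase in their perceived risk". Neither names a control condition.

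The Background subsection on perceived norms sets a different standard. It says that "the current study will include perceived drinking norms as a hypothesized mediator of the impact of the personalized feedback pamphlet intervention", and that if norms are the mechanism, then for the intervention to work "it must modify recipients' perceptions of how much others actually do drink".

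The Design section has respondents "administered a second telephone interview assessing the same drinking and mediator terms as the baseline survey" at three months. The three-month survey section repeats that "Mediator variables, perceived drinking norms and perceived risk will be measured using the same items as on the baseline survey" and times that survey for the control condition too. The Analysis Plan names structural equation modelling (SEM) with full information maximum likelihood, after two cited studies, and writes out no mediation paths.

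**The concern.** Mediation makes two claims: the randomised intervention shifts the mediator, and the shifted mediator carries the effect to the outcome. Hypotheses 3 and 4 address only something like the second, and only among recipients. They pick out people in whom the mediator moved for any reason. The design rationale concedes that some respondents will never see the pamphlet, so some changers in the arm may not have been exposed to it.

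Membership of the compared groups is settled after randomisation, in the same interview that records three-month drinking. Someone who has cut down for unrelated reasons may both report a lower norm and still be drinking less at six months. The same pattern would be expected in the no-intervention arm, which the stated comparison leaves out.

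Preliminary Study # 1 is criticised in the article because perceived risk was measured only after the intervention. Measuring at baseline and three months repairs the time order. It does not make changers and non-changers comparable.

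At stake is the mechanism claim: a positive Hypothesis 3 or 4, tested as worded, could be reported as how the pamphlet works even if the pamphlet did nothing.

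**Working it through.** **The plan's own figures.** Inputs from Power Analyses: 1% of variance (f = 0.10, or d = 0.20 for two groups), 80% power, 0.05 level, 390 per condition.
- Normal approximation, two-sided: n = 2 × (1.960 + 0.842)² / 0.20² ≈ 393 per arm.
- 1-df F test for an R² increase of 0.01: 779 in total for two arms, or 389.5 per arm. The stated 390 reproduces.
- Mediator and moderator power, from a 9% increase in variance: f² = 0.09/0.91 = 0.0989. Even in one arm, the noncentrality is 390 × 0.0989 = 38.6 and power exceeds 99.99%. The stated figure reproduces, but as power to detect an association. The 9% was a moderator effect of perceived risk in a post-test-only pilot.

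**Check 1: Hypothesis 3 with an inert pamphlet.** One arm of 390, 2,000 runs per setting. Assumptions, none from the article:
- Own drinking loads 0.7 on a stable trait, with correlated residuals between waves.
- The norm estimate correlates r with own drinking at the same wave, plus independent error.
- Fallers are compared with non-fallers on six-month drinking, adjusted for baseline drinking.
- Support means a favourable direction with two-sided p < 0.05, so the nominal rate is 2.5%.

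Ranges cover repeated runs:

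| Residual correlation between waves | r = 0.2 | 0.3 | 0.4 | 0.5 |
|---|---|---|---|---|
| 0 from baseline to month 3; 0.5 from month 3 to month 6 | 25–27% | 50–52% | 76–78% | 93–95% |
| Equal for successive waves (0.5 or 0.2) | 11–14% | 21–25% | 35–41% | 54–63% |

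The first row treats two successive intervals differently without a stated reason, so the second is the more natural setting. If norms also have a stable personal component (half the residual variance) in the first setting, the rates rise to about 46%, 80% and 97% at r = 0.2, 0.3 and 0.4. Adding three-month drinking as a covariate returned the rate to about 2–3% at every r, in a model where norms respond only to current drinking.

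**Check 2: a more general model.** Let ρ be the correlation, from other causes, between mediator change and drinking improvement. Half the arm are changers, and the pamphlet does nothing. The expected standardised difference is 2 × 0.798 × ρ.
- At ρ = 0.20 the difference is 0.319. Its standard error is 0.987 × 2/√390 = 0.100, so z = 3.19 and the chance of support is Φ(3.19 − 1.96) = Φ(1.23) = 0.89.
- Simulation with 4,000 runs gave 2.4%, 12%, 35%, 66%, 89% and 99.6% at ρ = 0, 0.05, 0.10, 0.15, 0.20 and 0.30.
- A two-arm analysis that also needed an arm-to-mediator effect (both paths p < 0.05) was falsely positive in 0.3% to 5.8% over the same range.

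The 9% in Power Analyses corresponds to a correlation of √0.09 = 0.30. At that association from common causes, the within-arm test is positive in over 99% of trials of an inert pamphlet.

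**Hypothesis 4.** It was not simulated in its own right. Check 2 applies only if common causes push risk up and drinking down, as motivation to change might. People who have already cut down may instead feel less at risk, which pushes the contrast the other way.

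**The case against.** The strongest reply is that the Aim section states predictions in prose and the analysis is set elsewhere. The Analysis Plan follows two cited accounts of SEM for experimental studies. The Background states the arm-to-mediator requirement for norms and gives a matching rationale for risk, and the mediators are measured in the control conditions. A conventional mediation model with all arms is therefore quite possible. This stands: a reader might infer that the final model omits the control arms, and the article does not show that. What remains is that the only contrast the article writes out is the within-arm one. If the model is the conventional one, the two hypotheses misdescribe it.

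Three further inferences go beyond the text.
- That change will be cut at zero in the analysis: no dichotomising rule is fixed, perceived risk is a six-item scale, and SEM takes continuous variables.
- That Hypotheses 3 and 4 are both biased towards confirmation: for Hypothesis 4 the direction is open.
- That a positive contrast would be empty: with the mediator measured before six-month drinking, it informs the mediator-to-outcome path, though only observationally.

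It is also fair that the abstract makes mediation secondary, and that the false-support rates depend heavily on assumed correlations.

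**Conclusion.** The point holds for the hypotheses as worded. They compare self-selected groups of intervention recipients, do not test whether the pamphlet moves norms or perceived risk, and so fall short of the article's own condition for mediation by norms.

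For Hypothesis 3 the inflation is in a clear direction but of uncertain size: roughly 10% to 95% false support for r between 0.2 and 0.5, against 2.5% nominal. That range is illustrative and not a bound, because r, the wave-to-wave correlations and the covariates are all assumed. For Hypothesis 4 the bias could go either way.

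The randomised comparisons in Hypotheses 1 and 2 are untouched, and no sample-size figure changes. A reader might conclude that the trial's mediation analysis is invalid; the article does not support that, since its SEM may already hold the needed path. The wording should still be corrected before results are read as mechanism.

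**What to change.** Restate Hypotheses 3 and 4 as indirect effects of randomised arm (personalised feedback pamphlet against each control condition) on six-month drinking through the continuous three-month mediator. Adjust for baseline mediator and baseline drinking, and use all three arms.

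Report the arm-to-mediator effect and a confidence interval for the indirect effect. State that the mediator-to-outcome path is observational. A rule that the arm-to-mediator effect must be separately significant is a matter of convention and is not essential.

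Show adjustment for three-month drinking as a sensitivity analysis. It guards against earlier drinking change driving the mediator, but may also remove mediation already realised by month three, when Hypothesis 1 expects an effect.

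Do not present the >99% figure in Power Analyses as power for the indirect effect.

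The cost is two reworded hypotheses, slightly more analysis and a more cautious mechanism claim. The mediators are already in the three-month survey for every arm, and SEM is already the method.

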### Design

In an initial telephone interview, sociodemographic information will be collected. Current drinkers will complete a standardized epidemiological assessment of problem drinking and alcohol consumption, and will answer items to assess their perceived drinking norms, their perceived risk regarding drinking and their social reasons for drinking. Respondents identified as problem drinkers will be asked if they are willing to participate in a three-month and a six-month follow-up. Respondents will be offered a $20 honorarium for completion of each of the three-month and six-month follow-ups. Verbal informed consent will be gathered and respondents will be told that some households will be receiving a pamphlet. Problem drinking will be defined as a score of eight or more on the Alcohol Use Disorders Identification Test (AUDIT) [64,65]. The initial telephone survey will be conducted with a random sample of respondents from households within a major metropolitan city in Canada. One current drinker 19 years or older (legal drinking age in Ontario, Canada) will be selected to participate from each household by soliciting participation from the adult in the household who had the most recent birthday who also drinks alcohol at least once per month. All households with respondents agreeing to participate in the follow-up interviews will be randomized into three groups – personalized feedback pamphlet condition, control pamphlet condition and no intervention control condition. In the week after the baseline survey, all households that contain respondents in the two pamphlet conditions will be sent their respective pamphlets. Three months after the intervention mailing, respondents who agree to the follow-ups will be administered a second telephone interview assessing the same drinking and mediator terms as the baseline survey (modified to refer to the past three months). Similar drinking outcome measures will be made six months after the intervention mailing with the items framed to refer to the past three-months. In order to ensure that all study participants receive some form of intervention, households in the no intervention control condition will be sent the personalized feedback intervention pamphlet after the six-month follow-up.

#### Rationale for the choice of study design

Why do we believe that the proposed study design is the best for testing the impact of this personalized feedback pamphlet? The intent of this project is to evaluate an ultra-brief intervention for problem drinkers that can be used in public health initiatives. As such, it is important that the intervention pamphlet be evaluated in a setting that mimics how it will be used. Thus, the pamphlets will be sent addressed to the household rather than addressed to the respondents because public health initiatives are often non-specific in their target recipients. The proposed research design has the advantage of allowing the pamphlet to be sent to all households in the intervention condition, irrespective of whether any of the respondents are specifically interested in receiving self-help materials. In order to conduct a study where intervention materials are sent directly to the person by name, for ethical reasons the respondent must at least state that he or she is hypothetically interested in receiving such materials. A study in which materials are sent unsolicited to households has been judged ethical because receiving such materials unsolicited (and unaddressed to a specific individual) is not an unusual occurrence given that public health initiatives are ongoing in the Toronto metropolitan area. However, informed consent is given because all respondents are told about the possibility of their household receiving the pamphlet. Further, it is important to be able to send materials to all households because interest in self-help materials covaries with respondents' perceived risk. In the pilot study described above, 76% of problem drinkers who perceived no risk associated with their drinking were not interested in self-help materials. This group comprised 32% of all problem drinkers in the sample. Thus, although the proposed method reduces the power of the intervention because not all respondents will see the pamphlet, it is still the best design for our purposes because it allows recruiting some problem drinkers with no perceived risk regarding their alcohol consumption. Studying the reactions of problem drinkers who do not perceive any risk associated with their drinking to intervention materials is of great importance because results from the pilot study for this proposal (Study 1 in the preliminary studies section) indicated that this group could react to the intervention materials by drinking more. Although the results of Study 1 were not conclusive because of its post-test only design and the fact that this 'boomerang' effect in reaction to the materials was a trend rather than a statistically significant result, we feel that the study of these types of unintentional effects is essential. The personalized feedback pamphlet is intended for wide distribution in the general public. If we confirm that this ultra-brief intervention can have a negative impact on some sub-groups of problem drinkers then this finding would speak to the need to target the intervention to only those drinkers who already voice some concern regarding their drinking. As there is insufficient evidence to-date that could confirm or refute this hypothesis, we feel that the need to test this hypothesis appropriately outweighs the potential ethical dilemma of causing a small unintended increase in alcohol consumption among a population of drinkers who are not seeking treatment and who meet criteria for a rather liberal definition of problem drinking (AUDIT score of 8 or more).

### Informed Consent Procedure

The study was approved by the standing ethics review committee of the Centre for Addiction and Mental Health. Telephone calls will be made by trained interviewers from the Institute of Social Research at York University (Toronto). The interviewers will introduce themselves, indicate they are calling from York University and that they are calling on behalf of the Centre for Addiction and Mental Health, which is conducting research on drinking. They will determine the number of monthly drinking adults in the household, randomly select one of them (according to most recent birthday) and before they start the interview they will read the following script:

"I would like to assure you that all information you provide, including your answers, identity, and any other information will remain completely confidential. You do not have to answer any questions you do not want to and if you decide to stop the interview, and wish us to do so, we will destroy all the information you have given us. On average, the interview will take about 15 minutes. Just to let you know, from time to time my supervisor may listen in to make sure we are doing the research correctly. The survey is voluntary, but your participation is very important if the results are to be accurate. Is now a good time to start the interview?"

At the end of the baseline survey, all problem drinkers (AUDIT ≥ 8) will be asked to participate in two, 15 minute surveys, the first in about three months time and the second in six months time. Participants will be offered $20 for the completion of each of the three-month and six-month follow-ups. Potential respondents will be told that these surveys will ask about their current drinking. Further, they will be informed that "the Centre for Addiction and Mental Health is in the process of mailing a safe-drinking pamphlet to some households in Toronto. I do not know if this pamphlet is being sent to your household, but if you do see it, the six-month follow-up survey will ask about your impressions of the materials." Respondents who agree to the follow-up will provide their name, address and telephone number. Because the baseline interview contact is made by telephone, verbal agreement to participate in the study will act as providing informed consent. Respondents will also be informed of the request to provide a collateral on the six-month follow-up at this time.

